## Abstract

**Background:**

Perioperative hypothermia during laparoscopy for bowel resection is a risk factor for postoperative medical complications and surgical wound infections. Despite various warming methods used during surgery, a significant number of patients experience perioperative hypothermia. Use of dry, unwarmed insufflation carbon dioxide (CO_2_) during laparoscopic procedures may contribute to this problem. Evidence exists that the HumiGard device, which humidifies and heats CO_2_ for insufflation, can reduce the risk of perioperative hypothermia.

**Objective:**

The aim is to determine if insufflation with warmed, humidified CO_2_ using the HumiGard device, alongside standard perioperative warming techniques, can improve patient recovery, including pain, surgical site infections, complications, and the use of analgesia compared with standard care alone.

**Methods:**

The study is a multicenter, randomized, blinded (patient, surgeon, and assessor), sham device-controlled, parallel group-controlled trial of 232 patients. The study aims to recruit patients undergoing elective laparoscopic, segmental, or total colectomy. Patients will be randomized to receive HumiGard plus standard care or standard care alone (1:1 ratio). The primary outcome is patient-reported quality of recovery, measured by the validated QoR-40 (quality of recovery) questionnaire, from baseline to postoperative day 1. Secondary outcomes include postoperative pain, the incidence of hypothermia, and the rate of postoperative complications.

**Results:**

The information gathered during a small-scale service evaluation at a single hospital was used to inform this study protocol. Before applying for a grant for this full randomized controlled trial, the authors will conduct a feasibility study of 40 patients to ensure that the protocol is feasible and to inform our sample size calculation.

**Conclusions:**

The randomized controlled trial is designed to provide high-quality evidence on the effectiveness of the HumiGard device in potentially reducing the risk of perioperative hypothermia in patients scheduled for laparoscopic colectomy. The results will be used to improve the maintenance of adequate patient body temperature during surgery.

**International Registered Report Identifier (IRRID):**

PRR1-10.2196/14533

## Introduction

### Intraoperative Hypothermia

Patients undergoing colectomy or intra-abdominal surgical procedures are at risk of developing perioperative hypothermia, defined as a core temperature less than 36°C [1]. General anesthesia is one of the contributing factors to the development of hypothermia due to the disruption of normal thermoregulatory responses. Evidence exists that perioperative hypothermia is associated with an increased risk of medical complications, morbid cardiac events, surgical would infections, and extended length of stay in hospital [2].

### Current Standard Practice in the United Kingdom

In the United Kingdom, the National Institute for Health and Care Excellence (NICE) recommends the following: (1) monitoring of patients’ intraoperative temperature every 30 minutes; (2) delaying the induction of anesthesia until the patient’s body temperature is greater than 36°C; (3) warming of intravenous fluids and blood products to 37°C; and (4) for procedures lasting longer than 30 mins, using a forced-air warming device lain on top of patients for warming [3].

Active warming methods do not guarantee that a patient will maintain an adequate body temperature. A recent study by Sun et al [4], which evaluated the core temperature of more than 58,000 actively warmed adults undergoing surgery longer than 60 minutes, showed that nearly half the patients developed hypothermia (body temperature <36°C) during the first hour of the procedure. Based on Lavies et al [5], the use of active warming methods reduced the perioperative incidence of hypothermia, but 53% of patients were still hypothermic in the postoperative phase.

During laparoscopic procedures, standard practice is to use dry, unwarmed CO_2_ to inflate the peritoneum (insufflation). This may contribute to the risk of hypothermia and cause tissue desiccation. Insufflation with unwarmed and dry gas can result in an additional drop in temperature by 1.3°C to 1.7°C [6] and potentially contribute to the risk of perioperative hypothermia.

### Intervention and Study Aims

HumiGard (Fisher & Paykel Healthcare, New Zealand) is a CE-marked medical device that humidifies and heats CO_2_ for insufflation. A meta-analysis of studies that evaluated this type of insufflation demonstrated a significant difference in mean core temperature change, a small beneficial effect on immediate postoperative pain (not at day 1 or 2), with potential impact on the incidence of hypothermia. No difference was observed in patients’ length of stay, analgesic consumption, and procedure duration [7,8]. In February 2017, NICE published guidance on HumiGard for preventing inadvertent perioperative hypothermia [9]. NICE found that the device showed promise, but that more research was needed before a decision could be made on routine adoption within the UK National Health Service (NHS).

This protocol is designed to address the evidence gaps identified by NICE. We aim to determine whether HumiGard used with other standard ways of warming patients results in better outcomes for patients compared with standard care alone. In addition, an economic evaluation will be carried out comparing the cost-effectiveness of HumiGard plus standard care with standard care alone.

## Methods

### Study Design and Population

The study is a multicenter, double-blinded (patient and assessor), sham device-controlled, parallel group randomized controlled trial (RCT). It aims to evaluate if the HumiGard insufflation device, along with standard care, can improve patient-reported quality of recovery (QoR) following laparoscopic colorectal surgery. The study will recruit patients undergoing elective laparoscopic colorectal resection for any pathology. The study is designed to be carried out in the colorectal departments of a minimum of four NHS hospitals across England and Wales.

On receiving the funding to carry out the RCT, the authors will seek a favourable opinion from Health and Care Research Wales and UK Research Ethics Committee. The trial will be registered on ClinicalTrials.gov. The protocol was prepared according to the CONSORT 2010 checklist for reporting parallel group RCTs.

### Eligibility Criteria

The inclusion and exclusion criteria for patients are presented in Textbox 1.

All emergency procedures will be excluded from the study because the presence of sepsis or infection, which affects core temperature, is an additional complication during emergency procedures.

Patient inclusion and exclusion criteria.
**Inclusion criteria**
Adults 18 years or olderScheduled for elective laparoscopic, segmental, or total colectomyAble to give informed consent
**Exclusion criteria**
Patients unable to complete study documentationPatients that lack the capacity to give informed consentPatients with a planned open laparoscopic procedureLaparoscopic surgery that is converted to open surgeryAll emergency procedures

### Interventions

During randomization, patients will be allocated to either the treatment arm or control arm of the study at a 1:1 ratio. Patients in the treatment arm will receive humidified and heated CO_2_ insufflation gas into the peritoneal cavity using the HumiGard device. These patients will also receive standard intraoperative warming methods, including warmed fluids and blood products, forced-air warming devices, and warmed blankets at the clinician’s discretion.

Patients in the control arm will be treated with a sham device plus standard intraoperative warming methods, including warmed fluids and blood products, forced-air warming devices, and warmed blankets at the clinician’s discretion. The sham device used in the standard care arm will be the same HumiGard device as is in the intervention arm; however, the sham device will be turned “off” so that the gas delivered to the peritoneal cavity for insufflation is not heated or humidified. The sham device will deliver CO_2_ (as is the case for current standard practice in the hospital) through the HumiGard tubing. The sham device will look and sound the same as the active intervention arm.

### Randomization and Blinding

A member of the research team will telephone the randomization service when a new participant has given signed informed consent to take part in the study to allow randomization to occur. This will occur on day 0 of the study (usually the morning of surgery). Randomization will happen after the patient has consented but before entry into the operating theater. This member of the research team will become unblinded to the allocation of that patient and will not be involved in data collection for that particular patient from the point of randomization onward. Randomization to one of two groups (HumiGard or sham device) will be carried out using a minimization program [10]. Minimization takes into account additional patient information, such as American Society of Anesthesiologists (ASA) grade, gender, and benign or malignant procedure type, to ensure even distribution of patients between treatment groups based on prognostic factors. The unblinded member of the research team will set up the HumiGard device or sham device ready for use according to the allocated group. Neither the patient nor the operating team will be aware of the treatment allocation.

### Clinical Outcomes

The primary outcome measure is the change in patient-reported QoR-40 (quality of recovery) scores from baseline to postoperative day 1 (POD 1).

The QoR-40 is a widely used and validated questionnaire that provides a patient-reported measure of recovery following surgery and anesthesia [11]. The questionnaire includes 40 items separated across five dimensions: patient support, comfort, emotions, physical independence, and pain. The QoR-40 is a reliable and valid tool for assessment of the quality of recovery in patients. It has very high acceptability among patients and is highly sensitive to any clinical changes [12].

The secondary outcomes for this study are:

Change in QoR-40 scores from baseline to POD 3.Change in patient-recorded pain scores from baseline to POD 1 and POD 3 using a visual analog scale (VAS). The score will range from 0 to 100.The incidence of hypothermia during the surgery (body temperature drop to 36°C during the procedure as recorded in the patient’s notes).Duration and depth (overall minimum temperature) of hypothermia.The rate of postoperative complications recorded at POD 1, POD 3, at discharge, and at POD 30. The severity will be assessed with the Clavien-Dindo scale, which is widely used for grading the severity of surgical complications in patients [13]. The Comprehensive Complication Index will be used later to create a composite score (0-100) for each patient [14].The incidence of site surgical infections within the first 30 days postsurgery.Length of stay in hospital from procedure to discharge (or until medically fit to discharge).Resource use outcomes, including analgesia (type and dose), use of strategies to maintain perioperative normothermia (eg, warming blanket, fluid warmer), time to discharge, length of procedure, length of recovery time, and readmission to hospital.Cost-effectiveness analysis of the HumiGard device compared with standard care.

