### The Study Process and Data Collection

The flowchart of the study process is presented in Figure 1.

At baseline, patient history, including age, gender, body mass index, smoking status, comorbidities, primary diagnosis, and ASA grade, will be collected. The patient questionnaires and VAS scale will be administered at baseline, POD 1, and POD 3 to patients with no knowledge of their treatment allocation. On arrival at the anesthetic room and during the procedure, the temperature will be measured using a urinary temperature probe.

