### Data Analysis

The statistical analysis plan will be followed for all clinical and economic analyses. Intention-to-treat analysis, the primary analysis method, will take into account minimization factors and sites. Whenever possible, standard errors, confidence intervals, and *P* values will be reported for outcomes.

Assuming a normal distribution of the data, the change in QoR-40 between groups will be analyzed with ANCOVA (analysis of covariance) while controlling for the baseline. The logistic regression for incidence rates will be used to compare the incidence of hypothermia between groups. ANCOVA will be used to compare the duration and depth of hypothermia and the Comprehensive Complication Index scores between groups. The incidence of surgical site infections, length of stay and procedure, and readmission rates will be summarized with descriptive statistics.

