**Intraoperative data**			
	**Temperature at arrival to theater, n (%)**		
		<36°C	2 (29)
		>36°C	3 (43)
		Unknown	2 (29)

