	**Temperature at the end of surgery, n (%)**		
		<36°C	2 (29)
		>36°C	5 (71)
		No change during surgery	2 (29)
		Higher (range 0.3°C-1°C) than at arrival	3 (43)
	Complications (during hospital stay), n		0
	Surgery time (hours), mean (range)		3.33 (1.58-4.17)

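### Depth and duration of hypothermia have no stated start point, so readings taken before insufflation, which the device cannot affect, may enter both secondary outcomes and weaken the comparison

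*Protocol article*

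**What the plan says.** Four places in the protocol article bear on this.

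- **Clinical Outcomes** restricts incidence to the operation: "The incidence of hypothermia during the surgery (body temperature drop to 36°C during the procedure as recorded in the patient’s notes". The next item is "Duration and depth (overall minimum temperature) of hypothermia". It repeats no window, and it does not say whether it covers every patient or only those who became hypothermic.
- **The Study Process and Data Collection** sets when readings are taken: "On arrival at the anesthetic room and during the procedure, the temperature will be measured using a urinary temperature probe".
- **Interventions** shows how the device acts: "Patients in the treatment arm will receive humidified and heated CO_2_ insufflation gas into the peritoneal cavity using the HumiGard device". Control patients are insufflated through the same equipment, switched off.
- **Data Analysis** states: "ANCOVA will be used to compare the duration and depth of hypothermia and the Comprehensive Complication Index scores between groups". That sentence names no baseline temperature. The section elsewhere provides for minimization factors and sites.

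Two further places bear on size. Table 1 (Service Evaluation) gives arrival and end-of-surgery temperatures for a few patients. The section on current UK practice cites an additional fall of 1.3 to 1.7°C with unwarmed, dry gas.

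**The concern.** The recorded series begins before treatment can act. A minimum reached before insufflation is the same whichever arm the patient is in. The better the device works, the more often the earlier reading becomes the lowest one.

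Take an invented patient who arrives at 35.6°C and whose lowest value after insufflation is 35.9°C. The overall minimum is 35.6°C. If the device had raised the later low by 0.3°C to 36.2°C, the score would still be 35.6°C, and the benefit would not register.

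Duration behaves differently. Time below 36°C before insufflation has the same expectation in both arms, so it leaves the expected difference in minutes unchanged. It adds variance and shrinks any relative difference.

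These outcomes are among the most direct measures of the device's mechanism, and the article's conclusions present the trial as evidence on reducing perioperative hypothermia. A diluted depth comparison could be misread as little effect on temperature.

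**Working it through.** The article gives no effect size, SD or power for depth, so there is no figure of its own to reproduce.

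**Step 1: what Table 1 can show.** Arrival temperature was below 36°C in 2 patients, above in 3 and unknown in 2. Among those known, 2/5 = 40%, exact 95% interval 5% to 85%. At the end of surgery 2 were unchanged and 3 are listed as "Higher (range 0.3°C-1°C) than at arrival". Since 2 + 3 = 5, these appear to be the five with a known arrival value, none of whom ended colder (5/5, exact 95% interval 48% to 100%). Neither the lowest value during surgery nor the time of insufflation is reported. A patient who ended warmer may still have been coldest mid-operation.

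**Step 2: a model for depth.** Let P be the lowest pre-insufflation value and Q the lowest value afterwards. In control patients Q − P = D, normal with mean m and SD s. The device adds τ to Q. Then

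overall minimum = min(P, Q) = P + min(0, D)

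E[min(0, D)] = m·Φ(−m/s) − s·φ(m/s)

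The expected difference between arms is this expression at m + τ minus its value at m. P cancels, so the share of the effect that is kept depends only on m, s and τ. It also follows that adjusting for P reduces variance but does not restore the lost difference.

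**Step 3: one case by hand.** Take m = 0, s = 0.3, τ = 0.3 (assumed).

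- Control: −0.3 × 0.399 = −0.120.
- Device: 0.3 × 0.159 − 0.3 × 0.242 = −0.025.
- Difference: 0.095°C, and 0.095/0.3 = 32% of the effect on the post-insufflation minimum.

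**Step 4: the range.** Assumptions: τ = 0.3°C, s from 0.3 to 0.5°C, P with mean 36.2°C and SD 0.4°C. Power is unadjusted, with the 116 per arm given under Sample Size Estimation. For the post-insufflation minimum it is 95% (s = 0.5) to about 100% (s = 0.3).

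| m, control (°C) | Minimum is pre-insufflation, control | Same, device | Effect kept | Power, overall minimum |
|---|---|---|---|---|
| −1.5 | 0% | 0–1% | 100% | 95–100% |
| −1.0 | 0–2% | 1–8% | 95–100% | 94–100% |
| −0.5 | 5–16% | 25–35% | 75–87% | 86–99% |
| −0.25 | 20–31% | 54–57% | 58–62% | 72–88% |
| 0 | 50% | 73–84% | 32–38% | 40–46% |

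At m = 0 the loss is 62% to 68%, about two thirds. A mean rise (m = +0.25) would keep only 10% to 21%. I do not use it as the end of the range, because the article gives no ground for a post-insufflation low that is on average above the pre-insufflation low. A larger τ would move more device-arm minima to before insufflation.

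**Step 5: a second model.** An explicit time course (arrival mean 36.1°C, SD 0.45; net rise of 0.3°C by 200 minutes; readings every 30 minutes; insufflation at 45 minutes; device gain up to 0.3°C) keeps 75–79% at an intraoperative dip of 0.4°C, 90–91% at 0.6°C, 97% at 0.8°C, 99% at 1.0°C and essentially all at 1.3 to 1.7°C. At dips of 0.2 and 0°C its results are unstable (55–66% and 35–60%), and I do not rely on them. The pattern agrees with Step 4.

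**The case against.** **The window belongs in the analysis plan.** The article is condensed and says a statistical analysis plan will be followed. That plan may fix the window, and the absence of detail alone would be no finding. But the article does state a definition of depth, and the definition is an overall minimum. A plan that follows it faithfully would count early readings.

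**The text has a narrower natural reading.** The preceding item confines hypothermia to the operation, and the data-collection section separates the arrival reading from those taken during surgery. Depth and duration may refer to that same intraoperative hypothermia. This is fair, and it would exclude the arrival value. It still leaves the interval between induction and insufflation.

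**The problem may be negligible.** If the cited additional fall of 1.3 to 1.7°C held for control patients here, nearly all control minima would come after insufflation and almost nothing would be lost. This stands, and it is why nil belongs in the range.

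**The consequence is limited.** The outcomes are secondary, randomization keeps the comparison valid, type I error is not inflated, and no sample size rests on them. All of this stands.

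A reader might go further and infer that for many patients the outcome is a pre-insufflation value, or that the effect is understated by a definite amount such as 9–40%. The documents do not support either. The first rests on five patients with no reported intraoperative low. The second follows from limiting the assumed dip to 0 to 0.6°C.

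**Conclusion.** The point holds as a defect in the definition. Neither measure has a start, recording begins before the device can act, and the rule admits readings that treatment cannot change. Any effect on depth is toward no difference; for duration it is added noise.

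The size cannot be determined from the article. With a device effect of 0.3°C and s of 0.3 to 0.5°C, the loss in depth is 0–5% if control temperatures fall by 1.0 to 1.5°C after insufflation, and about two thirds if there is no net fall. Table 1 and the cited fall with dry gas point in different directions, and neither gives the timing of the lowest temperature. How often a pre-insufflation reading would be the minimum therefore remains open. The change is worth making because it is cheap and must be made before data are collected. The primary QoR-40 analysis is not touched.

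**What to change.** - Define depth as the lowest temperature, and duration as the time below 36°C, from the start of CO2 insufflation to a stated end such as the end of surgery.
- Apply both to all randomized patients, with duration zero for those never below 36°C. This avoids comparing only those who became cold, a subset that treatment can itself alter.
- Record the insufflation start time on the case report form. The 40-patient feasibility study is a natural place to begin, since a time not recorded may not be recoverable later.
- Use the arrival or last pre-insufflation temperature as a baseline covariate in the ANCOVA, and keep it out of both outcomes. Arrival temperature was unknown in 2 of 7 service-evaluation patients, so the source of the baseline value should be settled in advance.

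Both arms are insufflated, so the start point applies equally to each. The cost is a sentence in the outcome definitions, one recorded time and one covariate. The small downside is that cold exposure before insufflation would be reported only descriptively. A rule is also needed for any randomized patient who is never insufflated.

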### Sample Size Estimation

Assuming a normal distribution of the data, we calculated that 232 patients (116 in each arm) will be required for this study. This number is based on detecting the minimum clinically important difference for the QoR-40 questionnaire of 6.3 with a standard deviation of 14.0 (Myles et al [15]). The standard deviation is high compared with more recent studies, such as Moro et al [16]. The study is powered at the 90% level with a 5% significance level. We allowed for 10% of patients lost to follow-up (for QoR at 24 hours) despite the fact that questionnaires will be issued while a patient will be still in hospital. The final recruitment target of 258 will be split into two cohorts of patients (two arms) of 129 patients each.

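### The stated inputs need 104 to 105 evaluable patients per arm, not 116; the 10% loss appears to be counted twice, and the 258 target conflicts with the abstract's 232

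*Protocol article*

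**What the plan says.** The Sample Size Estimation section says "we calculated that 232 patients (116 in each arm) will be required for this study". It ties that figure to the "minimum clinically important difference for the QoR-40 questionnaire of 6.3" "with a standard deviation of 14.0", and adds: "The study is powered at the 90% level with a 5% significance level". The 10% allowance for missing 24-hour questionnaires comes after this, and the section ends: "The final recruitment target of 258 will be split into two cohorts of patients (two arms) of 129 patients each". In this section, then, 232 is the number needed before attrition and 258 is the number to recruit.

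The Methods paragraph of the abstract describes a "parallel group-controlled trial of 232 patients" and does not mention 258.

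**The concern.** The section gives every input needed to check its result, and the result does not follow. A two-arm comparison of means with these inputs needs just over 100 patients per arm. The stated 116 is what remains after one 10% loss allowance has been added, yet the text presents it as the requirement before that allowance and then inflates again.

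Three statements are then out of step: the required number, the power and the recruitment target. If 232 is the evaluable number, power is about 93%, not 90%. If 232 is the recruited number, as the abstract suggests, 258 is wrong. A funder or ethics committee would see two trial sizes 26 patients apart, with no stated reason for the larger one. Every additional patient is randomized in a sham-controlled surgical trial, so the number needs a justification.

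**Working it through.** **Inputs.** From Sample Size Estimation: difference 6.3, SD 14.0, power 90%, significance level 5%, loss 10%, normally distributed data. From Interventions: 1:1 allocation. Sidedness is not stated; two-sided is assumed, and one-sided is tried below.

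**1. Evaluable patients per arm.**

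- Normal formula: n = 2 × (1.960 + 1.2816)² × (14.0/6.3)² = 2 × 10.507 × 4.938 = 103.8, rounded up to 104 (208 in total).
- t-test: 104.7, rounded up to 105 (210 in total).

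The protocol's 116 is not reproduced.

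**2. One 10% loss allowance, n/(1 − 0.10).**

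- 104/0.9 = 115.6, rounded up to 116 per arm, 232 in total. These are the protocol's figures for patients required.
- 105/0.9 = 116.7, rounded up to 117 per arm, 234 in total.

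**3. A second 10% allowance.**

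- 116/0.9 = 128.9, rounded up to 129 per arm, 258 in total. These are the protocol's recruitment figures.

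**4. Power at the stated difference and SD (two-sided 5%).**

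| Evaluable per arm | Normal formula | t-test |
|---|---|---|
| 104 | 90.1% | 89.8% |
| 105 | 90.3% | 90.1% |
| 116 | 92.9% | 92.7% |
| 129 | 95.1% | 95.0% |

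**5. Could 116 be a genuine evaluable number?**

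- One-sided 5%: 85 (normal) or 86 (t-test) per arm, further away.
- Rank-test allowance of π/3: 103.8 × 1.047 = 108.6, or 104.7 × 1.047 = 109.7, so 109 to 110. The worst-case efficiency of 0.864 gives 120.1 to 121.2, so 121 to 122. Neither is 116, and the section assumes normality.
- Baseline-adjusted ANCOVA, named under Data Analysis, would if anything lower n.
- Changed inputs, normal formula: 116 per arm at 90% power needs an SD of √(116/2) × 6.3/3.2415 = 14.8, or a difference of 3.2415 × 14.0 × √(2/116) = 5.96.
- Difference rounded down to 6.0: 2 × 10.507 × (14.0/6.0)² = 114.4, so 115 by the normal formula; the t-test gives 115.4, so 116. This reaches 116, but with a difference the section does not state.

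**6. Excess over the stated requirement.** 258 − 232 = 26 (26/232 = 11%); 258 − 234 = 24 (24/234 = 10%).

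**The case against.** **Double inflation is an inference.** The text shows no division, and sidedness, test and software are not given. The chain 104, 116, 129 fits at both steps, but a matching number is not proof. A t-test on a difference of 6.0 also gives 116, and a single allowance then gives 129. This stands as a caution about the cause. It does not rescue the section, which states 6.3, and 6.3 does not give 116.

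**The error is conservative.** 116 evaluable per arm meets and exceeds 90% power, and neither type I error nor the validity of the analysis is affected. This stands and limits the seriousness.

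**The surplus may be needed.** Conversion to open surgery is listed as an exclusion, yet patients are randomized before entering theater, and the 10% covers only missing 24-hour questionnaires. The documents give no conversion rate. Taking 5% or 10% as assumptions, with 10% questionnaire loss on top:

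- Recruiting 234 leaves 234 × 0.95 × 0.9 = 200 or 234 × 0.9 × 0.9 = 190 evaluable.
- Recruiting 258 leaves 221 or 209.

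With 200 or 190 evaluable (100 or 95 per arm), t-test power is 88.6% or 87.0%. So 234 could fall slightly short if converted patients were dropped. But the protocol does not offer this as the reason for 258, and its primary analysis is by intention to treat, which would keep them. It is a reason to state the margin openly, not a defence of the arithmetic.

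**The body text already separates required from recruited, and the size is provisional.** The first is true of Sample Size Estimation but not of the abstract, which gives 232 unlabelled. As to the second, the 40-patient feasibility study is meant to inform the calculation, but it does not correct the figure now stated, and the error could carry into the funding application.

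**Conclusion.** The concern holds. On the protocol's own inputs, with a two-sided test, the requirement is 208 to 210 evaluable patients and, after one 10% allowance, 232 to 234 recruited. The stated figures are 232 and 258, which is 24 to 26 recruits (10 to 11%) more than the stated 90% power calls for. If 232 patients are evaluable, power is 92.7% by the t-test.

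Two parts are firm: 116 per arm does not follow from 6.3, 14.0, 90% and 5%, and the abstract and the sample size section give different, unlabelled trial sizes. Double counting of the 10% loss is the most direct explanation, since it needs no input beyond those stated, but it remains an inference. The excess is measured against the stated 10% loss alone and would shrink or vanish if converted patients were removed from the analysis. The error costs recruitment effort and clarity, not power.

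**What to change.** Rewrite the Sample Size Estimation paragraph as one chain and carry its recruitment figure into the abstract. Either of these is consistent:

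- **Keep 90% power.** 105 evaluable per arm (210) give 90% power to detect 6.3 points with SD 14.0 at two-sided 5%; allowing for 10% loss, 117 per arm (234) will be recruited. The abstract then says 234 recruited.
- **Keep 258.** Recruiting 129 per arm (258) is expected to leave 116 evaluable per arm after 10% loss, which gives about 93% power for 6.3 points with SD 14.0 at two-sided 5%. The abstract then says 258 recruited, and the text gives the reason for the margin.

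If the calculation in fact used another difference or SD, state that value in place of the present one. In every case, state that the test is two-sided, label each number as evaluable or recruited, and say whether patients converted to open surgery after randomization count as evaluable, because the choice between the two options partly depends on it.

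The cost is wording in two places. Neither option adds patients to the present target; the first reduces it by 24.
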